### Data analysis

Below, a general plan has been developed to analyze data on clinical effectiveness, economic evaluation and process evaluation. In order to conduct quantitative analyses, SPSS and R will be used. Nvivo, which is a coding software tool, will be used to convert and analyze qualitative data from the patient interviews. Data analyses will be conducted according to the intention-to-treat principle, meaning that analysis of all trial results is entirely based on the initial treatment arms to which all patients were assigned after randomization, regardless of whether they actually received that treatment or not. Data-analysts will be blind for condition. Covariates, including sex, age, prior treatment and gender, will be accounted for in all (baseline) analyses to ensure the comparability of both treatment arms after proper randomization. Lastly, a two-sided significance level of 0.05 will be applied to test statistical significance.

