#### Randomization

Random allocation to the control group (continued CBT-E) or the intervention group (GST) will be conducted separately for each treatment location in a ratio of 1:2 by an automatized randomization software program after the completion of the post measurement. This ratio is due to the cluster effect in group-based therapy, which statistically requires more participants for the GST arm than for the continued CBT-E arm. Subsequent to randomization, participants in the GST arm and continued CBT-E arm will complete a baseline measurement (T0). After that, both treatments will start. Post-measurements (T1) will take place on the known end date of the treatment to which a participant is randomized. Follow-up measurements will take place 6 months (T2) and 12 months (T3) later, following initial completion of the entire treatment trajectory at T1. Several clinical measurement instruments are used, see Fig. 1. The current study protocol has been approved by the Medical Research Ethics Committee (MREC) Academic Hospital Maastricht/University Maastricht in The Netherlands, which was formally registered as: NL80491.068.22. The study is registered at ClinicalTrials.gov (registration number NCT05812950), and complies with the World Health Organization Trial Registration Data Set. Modifications to the protocol will be submitted as an amendment and will be examined by the MREC and will be adjusted in the trial registry.

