### Sample size

In order to reliably measure the quantitative primary outcomes following completion of the GST treatment and continued CBT-E treatment, a two-tailed alpha of 5%, a power of 90% and a medium effect size of d = 0.50 is assumed. This yields a sample size of 86 patients per treatment arm, thus *N* = 172 in total for a classical RCT. However, there is clustering in the GST arm due to its group format for treatment delivery. Therefore, an additional design effect is needed to correct the GST sample size for potential clustering. Assuming a group size of 8 participants and an intra-class correlation of 0.10, a design effect of 1.70 was computed. When multiplying this design effect with the original sample size of the GST arm (*N* = 86), the adjusted necessary sample size for the GST arm is equal to 1.70 *86 = 146 participants. Adding the initial number of participants in the continued CBT-E arm (*N* = 86), the total number of necessary study participants is equal to *N* = 232.

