Subsequent to randomization, participants will complete measures before continued CBT-E or the start of GST (T0), immediately after the confirmed end date of treatment (T1), and 6 months (T2) and 12 months (T3) following completion of treatment. In addition to measuring perceived ED schemas, data on quality of life and healthcare service use will also be gathered on these occasions. Data on process evaluations, as assessed by session rating scales and patient registration files, will be collected during each treatment session of phase 1 CBT-E, continued CBT-E, and GST. After treatment (T1), a representative sample of ED patients from both arms will be recruited to participate in a qualitative interview to gain deeper insights into their treatment experiences. Due to the nature of the interventions, blinding of therapists, interviewers, and patients is not possible. Below, all measures are stratified for clinical effectiveness, economic evaluation and process evaluation.

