#### Clinical effectiveness

Using t-tests and Chi-square tests, differences between the GST arm and CBT-E arm regarding demographic and clinical characteristics will be described. Dropout analysis among patients will be corrected for relevant background characteristics in order to examine the representativeness of our study population during the trial. In case dropout is selective, follow-up analyses will take this phenomenon into account. Relevant background characteristics may include gender, age and diagnosis. After treatment, change scores will be determined in multilevel analyses for both treatment arms between T0 and T1, T1 and T2, and T2 and T3. Suitable model assumptions will be used in order to account for the potential measurement correlations between these time points and nested data structures. Likewise, the significance of change scores between both arms will be determined at each time point, using a regression based mixed models approach. In case of significant effects, suitable post hoc analyses will be conducted. If possible, clinical findings will be at least stratified for gender and age in both treatment arms. In order to examine the robustness of clinical findings, sensitivity analyses will be performed, including the analysis of missing data. Based on the intention-to-treat principle, missing value analysis in SPSS will be used in order to estimate expected values of missing outcomes among participants remaining in the analysis. Based on the quality, completeness and statistical distributions of the data obtained, suitable missing data handling procedures will be applied.

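### The unqualified statement that data-analysts are blinded cannot hold for the comparative analyses: 1:2 allocation and arm-specific treatment data reveal which arm is GST

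*Protocol article*

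**What the plan says.** The opening paragraph of Data analysis, which introduces the clinical, economic and process analyses together, states: "Data-analysts will be blind for condition". No mechanism is given and no analysis is excepted. It is the only blinding that the article claims, since Data collection says that "blinding of therapists, interviewers, and patients is not possible".

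The following parts of the article bear on whether the statement can be true:

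- **Allocation.** Randomization says that allocation is "conducted separately for each treatment location in a ratio of 1:2 by an automatized randomization software program", and gives the reason: "This ratio is due to the cluster effect in group-based therapy, which statistically requires more participants for the GST arm". Sample size plans 86 patients for continued CBT-E and 146 for GST.
- **Clustering.** Sample size says that "there is clustering in the GST arm due to its group format for treatment delivery". The Clinical effectiveness part of Data analysis says that nested structures will be modelled, without giving the form.
- **Treatment format.** GST has 26 weekly group sessions and may start up to three months after randomization. Continued CBT-E has 12 to 32 individual sessions.
- **Arm-specific analyses.** The economic evaluation builds intervention costs bottom-up in each arm. The process evaluation compares session ratings between the arms.
- **Open choices.** The Clinical effectiveness part of Data analysis says: "Based on the quality, completeness and statistical distributions of the data obtained, suitable missing data handling procedures will be applied". It also says that selective dropout, if found, will be taken into account in later analyses.

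**The concern.** A blind analyst must be unable to tell which coded arm is which. Here the arm counts alone give the answer, and other variables confirm it. The article therefore claims a property that its own design rules out for every analysis comparing the arms.

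The consequence concerns the choices left open until the data are seen. The trial is open-label, the primary outcome is a self-completed questionnaire (the EDE-Q), and the stated hypothesis is that GST is better. If the missing-data method or the handling of dropout is chosen by someone who can see which arm is GST, the choice can lean towards that hypothesis, even unintentionally. The trial report would also describe a safeguard that was not in place for the comparison.

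**Working it through.** **1. The plan's own arm sizes.** Inputs from Sample size: "a two-tailed alpha of 5%, a power of 90% and a medium effect size of d = 0.50 is assumed"; group size 8; intra-class correlation 0.10.

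- Patients per arm for a two-sample t-test: 86 (power 0.903, noncentral t).
- Design effect: 1 + (8 − 1) × 0.10 = 1.70.
- GST arm: 1.70 × 86 = 146.2, stated as 146.
- Total: 86 + 146 = 232, as stated.

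The GST share is 146/232 = 0.629 under the sample-size figures and 2/3 = 0.667 under the 1:2 ratio. Both are carried forward.

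**2. Can GST be recognised from arm counts alone?** Suppose the arms are labelled A and B, and each patient is allocated to GST independently with probability p. Independence is an assumption: the article does not describe blocking, and blocking would make recognition more certain. The number in GST is then X ~ Binomial(N, p), and the chance that GST is the larger arm is P(X > N/2).

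| N | p = 0.667 | p = 0.629 |
|---|---|---|
| 232 | > 0.9999998 | 0.99996 |
| 116 | 0.9998 | 0.997 |
| 60 | 0.994 | 0.972 |

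Swapping the labels does not help, because the counts appear in any tabulation by arm.

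**3. Other routes.** Session number and format, the possible wait before GST starts, and bottom-up intervention costs are specific to the arm. In particular, nobody can cost the two treatments without knowing who was assigned to or received each. Therapy-group codes would reveal GST as well, if they are supplied for that arm only.

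**4. What knowing the arms could do to the error rate.** This part is an illustration. Assume k defensible analyses whose z-statistics have a common correlation r under the null, and an analyst who reports the one most favourable to GST. The result is then M = max(z₁, …, z_k). By simulation:

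- Single prespecified analysis: P(z > 1.96) = 0.025; two-sided error 0.05.
- k = 3, r = 0.8: P(M > 1.96) = 0.049; P(|M| > 1.96) = 0.056. False findings against GST therefore fall to 0.056 − 0.049 = 0.007.
- Two-sided error for other assumed values: 0.053 for k = 3, r = 0.9; about 0.067 for k = 5, r = 0.8.

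The main effect is on direction: false findings in favour of GST about double (0.049/0.025 ≈ 2), while the two-sided rate moves little.

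**The case against.** Four points can be made for the plan.

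- **The article is condensed, and fixes a good deal.** It names the EDE-Q as the primary outcome, intention-to-treat analysis, a two-sided 0.05 level and a mixed-model approach. A full protocol or SAP that is not shown may fix the rest. This stands, and a reader who inferred that the analysis choices have no protection at all would go beyond the documents. It does not rescue the blinding sentence: an SAP can fix a model, but it cannot make arms of 86 and 146 unrecognisable.
- **The clustering argument is weak alone.** The article asks only that nested structures be modelled. Therapist or dummy cluster codes could be supplied in both arms, so fitting the model need not reveal GST. Session counts and costs belong to the process and economic evaluations, which another analyst may handle. This stands, but the allocation ratio is sufficient without either.
- **The error rate.** A reader might infer that the two-sided type I error rises to about 0.10. That is the chance that any of three tests (r = 0.8) exceeds 1.96 in absolute value (0.098). Picking the largest absolute z needs no knowledge of the arms, so a perfectly blinded analyst could do the same. It measures analytic flexibility and not the loss of the blind; the directed figures in the working are the relevant ones.
- **Reliance on the blind.** A reader might also infer that the plan leaves choices open because it trusts the blind to keep them neutral. The article draws no such link.

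Finally, some blinding is feasible. Missingness, completeness and distributions can all be examined on pooled data without arm codes, so the safeguard should be narrowed and not abandoned.

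**Conclusion.** The blinding statement is wrong as written for the comparative clinical, economic and process analyses. Recognition of GST from coded arm counts is practically certain (above 0.9999 at N = 232). That result rests on the plan's own figures and the assumption of independent allocation.

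The consequence is limited. Choices that the article leaves to the data could be made with the arms known. Under assumed values (three analyses, correlation 0.8, deliberate choice of the most GST-favourable), the false pro-GST rate goes from 0.025 to about 0.049 and the two-sided error to about 0.056. These figures show the scale of the risk and do not predict what the analysts would do. What is at stake is the credibility of the analysis choices and the accuracy of the report. The documents do not support a stronger claim that nothing protects the analysis or that the type I error doubles.

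**What to change.** - Limit the sentence in Data analysis to steps done on pooled data without arm, group or session codes: checks of missingness, completeness and distributions.
- At that stage, before arm-coded outcome data are released, fix and date the primary EDE-Q model, the missing-data method and the handling of selective dropout. Code may be developed on a dataset with permuted arm and group identifiers.
- Do not report the comparative clinical, economic or process analyses as analyst-blinded.

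The cost is a change of wording, a dated record and, if used, one permuted dataset. Choices that depend on the data must be settled earlier, and the general claim of blinded analysis is lost. Sample size, power and nominal alpha stay as they are.

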#### Clinical effectiveness

Using t-tests and Chi-square tests, differences between the GST arm and CBT-E arm regarding demographic and clinical characteristics will be described. Dropout analysis among patients will be corrected for relevant background characteristics in order to examine the representativeness of our study population during the trial. In case dropout is selective, follow-up analyses will take this phenomenon into account. Relevant background characteristics may include gender, age and diagnosis. After treatment, change scores will be determined in multilevel analyses for both treatment arms between T0 and T1, T1 and T2, and T2 and T3. Suitable model assumptions will be used in order to account for the potential measurement correlations between these time points and nested data structures. Likewise, the significance of change scores between both arms will be determined at each time point, using a regression based mixed models approach. In case of significant effects, suitable post hoc analyses will be conducted. If possible, clinical findings will be at least stratified for gender and age in both treatment arms. In order to examine the robustness of clinical findings, sensitivity analyses will be performed, including the analysis of missing data. Based on the intention-to-treat principle, missing value analysis in SPSS will be used in order to estimate expected values of missing outcomes among participants remaining in the analysis. Based on the quality, completeness and statistical distributions of the data obtained, suitable missing data handling procedures will be applied.

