**Methods:**

Using a multicenter RCT design, 232 Dutch (atypical) AN and BN patients with a CBT-E referral will be recruited from five treatment centers. Clinical effectiveness and cost-effectiveness will be measured before treatment, directly after treatment, at 6 and at 12 months follow-up. In order to rate process evaluation, patient experiences and the degree to which treatments are implemented according to protocol will be measured. In order to assess the quality of life and the achievement of personalized goals, interviews will be conducted at the end of treatment. Data will be analyzed, using a regression-based approach to mixed modelling, multivariate sensitivity analyses and coding trees for qualitative data. We hypothesize GST to be superior to CBT-E in terms of clinical effectiveness and cost-effectiveness for patients who do not show a rapid response to the first 4 weeks of a CBT-E treatment.

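### Stratifying the clinical findings by gender and age cannot show whether the GST effect differs between patients, and the trial is sized only for the overall contrast

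*Protocol article*

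**What the plan says.** The Clinical effectiveness part of the Data analysis section first plans multilevel change scores and between-arm significance at each time point, then post hoc analyses where effects are significant. The next sentence is "If possible, clinical findings will be at least stratified for gender and age in both treatment arms". The general opening of Data analysis states that "a two-sided significance level of 0.05 will be applied to test statistical significance", and it lists age, sex and gender only as covariates for adjustment. The Sample size section addresses a single comparison, GST against continued CBT-E in all randomised patients: "a two-tailed alpha of 5%, a power of 90% and a medium effect size of d = 0.50 is assumed". No gender mix, age mix or age cut-off is given.

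**The concern.** The article names a way of looking at gender and age, namely splitting the results, and that way does not answer the question a reader will bring to it. A result within women and a result within men each say whether an effect is visible in that group. Neither says whether the two effects differ. Adjusting for gender and age as covariates does not say so either.

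Because the trial is sized for the overall contrast, every stratum has less power than the whole, and a small one has very little. An effect that is the same in everyone can then look present in the larger stratum and absent in the smaller one through numbers alone. The article wants its results to guide care trajectories, policymakers and insurers (abstract Discussion; Implications for healthcare policy and clinical practice). A finding of the kind that GST works in women but not in men, or in younger but not older patients, could reach them without support.

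**Working it through.** **Inputs from the Sample size section.**
- Two-sided alpha 0.05, power 90%, d = 0.50. The outcome is standardised, so SD = 1.
- Size per arm before clustering: 86.
- Clustering, in the GST arm only: "Assuming a group size of 8 participants and an intra-class correlation of 0.10, a design effect of 1.70 was computed".
- GST arm after inflation: 146. CBT-E arm: 86.

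**Input that is assumed.** The share f of patients in the larger stratum. The article gives none, so I use 50/50 to 95/5.

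**Reproducing the plan.**
- The t-based size for d = 0.50, two-sided 5% and 90% power is 85.03, rounded up to 86 per arm.
- Design effect: 1 + (8 − 1) × 0.10 = 1.70.
- GST arm: 1.70 × 86 = 146.2, taken as 146. Total: 146 + 86 = 232. The plan's figure reproduces.
- Overall power with an effective 86 against 86 is 90.6%.

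**Stratum check.** The true effect is d = 0.50 in both strata. Each stratum is tested at two-sided 0.05, with power = Φ(0.50/SE − 1.96).

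*Model A: the 1.70 design effect applies within each stratum, as if each therapy group held one stratum only.* The strata are independent, with effective sizes 86f and 86(1 − f) per arm.
- 50/50: SE = √(2/43) = 0.216; power = Φ(2.318 − 1.96) = 0.640. Exactly one significant: 2 × 0.640 × 0.360 = 0.461.
- 80/20: SE = √(2/68.8) = 0.1705 and √(2/17.2) = 0.341; powers 0.835 and 0.311. Exactly one significant: 0.835 × 0.689 + 0.311 × 0.165 = 0.627.

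*Model B: therapy groups mix both strata and share a group effect.* There are 146/8 = 18.25 groups. The variance of the stratum difference is 0.10/18.25 + 0.90/(146f) + 1/(86f), and likewise with 1 − f. The covariance between strata is 0.10/18.25 = 0.0055.
- 50/50: variance = 0.0055 + 0.0123 + 0.0233 = 0.0411; power = Φ(2.467 − 1.96) = 0.694.
- The joint probability comes from 400,000 bivariate normal draws.

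| Split (assumed) | A: power, larger / smaller | A: exactly one significant | B: power, larger / smaller | B: exactly one significant |
|---|---|---|---|---|
| 50/50 | 0.640 / 0.640 | 46% | 0.69 / 0.69 | 39% |
| 60/40 | 0.719 / 0.545 | 48% | 0.762 / 0.609 | 41% |
| 70/30 | 0.783 / 0.435 | 54% | 0.812 / 0.503 | 47% |
| 80/20 | 0.835 / 0.311 | 63% | 0.852 / 0.370 | 57% |
| 90/10 | 0.875 / 0.178 | 74% | 0.883 / 0.216 | 71% |
| 95/5 | 0.892 / 0.110 | 81% | 0.895 / 0.132 | 79% |

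Using t rather than normal tests in model A raises its figures by about one point at most.

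**Sensitivity to loss.** The sample size steps contain no allowance for dropout. With 20% loss in both arms, the range from 50/50 to 95/5 becomes 50% to 76% (A) and 44% to 74% (B).

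**Comparison.** With no true difference between strata, a treatment-by-stratum interaction test at 0.05 signals one in about 5% of trials, by construction.

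**The case against.** The strongest reply is that the article commits to very little here. Its sentence is hedged, it sits in what the section calls a general plan, and it mentions neither a significance test per stratum nor a claim about strata. It could mean a descriptive table by gender and age within each arm. Age cut-offs, interaction terms and exploratory labels are matters that a statistical analysis plan usually settles, and that document is not at hand. The stated hypotheses concern the whole early non-responder population, and the policy aims mention no gender- or age-specific guidance.

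Much of this stands, and it limits the point in three ways.
- A reader might infer that the article plans a test in each stratum and will draw subgroup conclusions from it. The text does not say so. The percentages above describe what happens if the strata are read that way.
- A reader might infer that the strata would disagree at least half the time whatever the split. They would not: for equal strata the figure is 39–46%, and with mixed therapy groups it is still 47% at 70/30.
- A reader might count four strata as four formal tests and compute an inflated false-positive rate when GST has no effect. The documents plan no such set of tests.

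At 95/5 the smaller stratum would hold about 12 of 232 patients (0.05 × 232 = 11.6), about 4 of them in CBT-E (0.05 × 86 = 4.3). The article's own hedge might then rule the split out.

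What the reply does not remove is that stratification is the method the article names, directly after between-arm significance results and under an unadjusted 0.05 level. An analysis plan would have to replace that choice, not merely add detail to it.

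**Conclusion.** The point holds as a weakness in the chosen method, with medium confidence. Stratified findings alone cannot show whether the GST effect depends on gender or age, and the article links them to nothing that could.

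If strata are read by significance, a uniform d = 0.50 gives one significant and one non-significant stratum in about 39–46% of trials for equal strata and 57–81% for splits from 80/20 to 95/5, against about 5% false signals from an interaction test. These figures are for one two-level split and one contrast. They rest on the article's own d, ICC, group size and N, full follow-up, and assumed splits. The lower figure of each range has therapy groups mixing the strata, and the upper has them separate.

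The primary analysis and the sample size for the overall comparison are not affected.

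**What to change.** Replace the stratification sentence in the protocol or the analysis plan with:

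> Whether the treatment effect on the EDE-Q differs by gender or by age (continuous) is explored by adding gender and age interactions with the treatment effect at each time point to the mixed model (treatment-by-time-by-gender and treatment-by-time-by-age, or treatment-by-modifier per visit if baseline is a covariate), reported as estimates with 95% CIs. Stratum-specific effects are derived from that model and labelled exploratory, and no subgroup claim is made from significance within a stratum.

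The form of the terms matters. If baseline is modelled as a repeated outcome, a plain treatment-by-gender term describes a difference between arms at baseline, not a difference in treatment effect over time.

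The cost is a change of wording and a few extra terms in exploratory runs of the same model. No new data or patients are needed. The intervals will be wide, which fairly shows how little a trial of 232 can say about subgroups. The change is best made before outcome data are analysed by arm, so that it cannot appear driven by results.

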## Background

Eating disorders (EDs) are associated with decreased social, psychological, and physical functioning in individuals [1] and elevated premature mortality rates [2]. On a healthcare system level, EDs contribute substantially to the mental health burden. Between 2000 and 2018, the weighted mean of point ED prevalence across continents had increased from 3.5 to 7.8% [3].

In a similar vein, the collective ED disease burden is reflected through major socioeconomic constraints. On average, ED patients generate more healthcare expenses and have lower employment rates than people without ED [4]. According to Van Hoeken and Hoek [5], over 3.3 million healthy life years are lost worldwide annually due to EDs. In addition to that, these authors showed that ED patients generated a 48% increase in healthcare costs, compared to the general population, while EDs with comorbid other psychiatric disorders were associated with a 48% decrease in yearly earnings in those employed.

In clinical practice, enhanced cognitive behavioral therapy (CBT-E) is used as treatment for all types of EDs, because of its transdiagnostic applicability and effectiveness [6]. Even though CBT-E is clinically effective for a certain group of ED patients, it is presumably not the most clinically optimized treatment for patients with (atypical) Anorexia Nervosa (AN) or Bulimia Nervosa (BN). More specifically, CBT-E is characterized by a substantial dropout rate: 20–54% in randomized controlled trials [6], especially in AN [7–9]. In general, only 30–50% of ED patients achieve clinical remission after CBT-E treatment [6, 10].

Although certain ED patients are greatly capable of challenging their own belief systems during treatment, they are generally unable to modify deeply held core beliefs [11]. In line with this observation, many ED cases reflect a complex intertwining between eating pathology and comorbid personality pathology [11–13], including clinical perfectionism [14]. Moreover, comorbid personality pathology increases the risk of attrition and is associated with greater psychopathology after treatment [11]. Albeit uncertain, not all (atypical) AN and BN patients may benefit sufficiently from CBT-E, perhaps due to a lack of emphasis on deeply rooted core beliefs.

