### Operational challenges

Although we are confident about the general applicability and resilience of the current study protocol, there are certain operational challenges that require our consideration.

First, ED patients are at risk of comorbid physical and mental health complications [65]. Even though severely vulnerable and ill-protected ED patients will be excluded during the screening phase, we cannot rule out the possibility of ED patients terminating their research participation due to health complications in a subsequent research phase. As a result, there is an inherent risk of incomplete data, which we aim to address by conducting all statistical analyses according to the intention-to-treat principles. Additionally, information leaflets are tailored to the research treatment phases that apply to participating patients, supporting their treatment adherence.

Second, participating ED treatment centers could face implementation challenges due to several barriers [66], including financial constraints and management challenges on the organizational level. In order to address these issues, regular communication strategies and facilitation of the implementation processes are key. In light of this objective, we aim to organize regular meetings and we will establish consistent communication lines, both online and on-site. Newsletters are prepared regularly in order to convey important updates and to optimize the overall sense of community among our participating partners.

Third, completion of all measurements may require substantial efforts from participants. Given the number of relevant questionnaires being administered, a full measurement may take up to two hours to complete. Although encouraging visuals will be implemented digitally to facilitate completion of each measurement over an extended time span with regular breaks, completing all measurements in time may still be challenging for participants. If possible, completion of measurements will be supported on-site at the institutions.

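### The one missing-data method named is an expected-value fill-in: analysed as observed data it would understate standard errors, and its reference to those remaining must be reconciled with intention-to-treat

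*Protocol article*

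**What the plan says.** All of this is in the protocol article.

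- **Main comparison** (Data analysis, Clinical effectiveness): change between arms is tested at each time point "using a regression based mixed models approach".
- **Dropout** (same section): "In case dropout is selective, follow-up analyses will take this phenomenon into account". How is not stated.
- **Robustness** (same section): "sensitivity analyses will be performed, including the analysis of missing data".
- **The rule at issue**, which comes next and is introduced as following from intention-to-treat: "missing value analysis in SPSS will be used in order to estimate expected values of missing outcomes among participants remaining in the analysis".
- **The sentence after it**: "Based on the quality, completeness and statistical distributions of the data obtained, suitable missing data handling procedures will be applied".
- **Intention-to-treat** (Data analysis, opening paragraph): "analysis of all trial results is entirely based on the initial treatment arms to which all patients were assigned after randomization", whatever treatment was received.
- **Expected missingness**: Operational challenges says that "there is an inherent risk of incomplete data, which we aim to address by conducting all statistical analyses according to the intention-to-treat principles". The Background reports that "CBT-E is characterized by a substantial dropout rate: 20–54% in randomized controlled trials". No rate of missing outcomes is given for this trial.

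**The concern.** An expected value is a conditional mean. Putting it in place of a missing score adds a data point that lies exactly on the fitted model. The residual variance then shrinks, the apparent sample size returns to its full value, and the analysis reports more information than was collected. Multiple imputation avoids this through random draws and pooling, but the text mentions neither.

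Two further features of the wording add to the problem. Estimation is limited to those remaining in the analysis, although the sentence invokes a principle that the same article defines by all assigned patients. And the final procedure is to be picked in the light of the data obtained.

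At stake is the credibility of whichever EDE-Q analysis uses the filled values. If that is only a sensitivity analysis, it would seem to confirm a result with precision it does not have. If it is the main comparison, the type I error rate of the trial is affected.

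**Working it through.** **The plan's own figure.** The Sample size section uses d = 0.50, two-sided alpha 5% and power 90%. The t-test solution is 85.03 per arm, rounded up to 86. The design effect is 1 + (8 − 1) × 0.10 = 1.70, and 1.70 × 86 = 146.2, taken as 146. The total is 146 + 86 = 232, as stated. This confirms the arm sizes used below. It does not test the missing-data rule, for which the article gives no figure.

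**Inputs.**
- Arm sizes 86 and 146, from the Sample size section.
- Two-sided 0.05 level, from the Data analysis section.
- Missing fraction m: assumed at 10%, 20%, 30% and 54%. The values 20% and 54% are the ends of the dropout range that the Background gives for earlier CBT-E trials. Dropout from treatment is not the same as a missing EDE-Q, so these only span a range.
- Also assumed: correlation of 0.5 between baseline and outcome, data missing completely at random, no clustering.

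**Approximation.** Let σ² be the residual variance and n the number randomised.
- Filled values have zero residual, so the estimated residual variance is about (1 − m)σ², and the software divides by information from n patients. Reported variance is proportional to (1 − m)σ²/n.
- The estimate in truth rests on (1 − m)n patients. True variance is proportional to σ²/[(1 − m)n].
- Variance ratio: (1 − m)². Standard error ratio: 1 − m.
- Actual type I error: 2 × [1 − Φ(1.96 × (1 − m))].
- For m = 20%: 1.96 × 0.80 = 1.568, giving 11.7%. For m = 30%: 1.96 × 0.70 = 1.372, giving 17.0%.

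**Simulation.** 4,000 trials per setting under no treatment effect. Missing outcomes were replaced by predictions from arm and baseline, then analysed by ANCOVA as if observed.

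| Assumed missing | Mean reported SE | True SE | Ratio | Type I error, simulated | Type I error, approximation |
|---|---|---|---|---|---|
| 10% | 0.112 | 0.124 | 0.90 | 7.8% | 7.8% |
| 20% | 0.105 | 0.132 | 0.80 | 11.8% | 11.7% |
| 30% | 0.098 | 0.142 | 0.69 | 17.4% | 17.0% |
| 54% | 0.079 | 0.175 | 0.45 | 38.8% | 36.7% |

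On the same simulated data, ANCOVA of the observed outcomes alone, with nothing filled in, rejected in 4.6% to 5.1% of trials at every missing fraction. The excess therefore comes from the filling in and not from the missingness.

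**The analysis population, by text.** The intention-to-treat definition covers every assigned patient. The fill-in sentence covers those remaining. These agree if remaining means kept in the intention-to-treat set. They disagree if it means not having left the study. Operational challenges expects some patients to end their participation and offers intention-to-treat as the answer, so the status of exactly those patients is left unclear.

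**The case against.** The strongest reply is that the sentence carries less weight than the arithmetic suggests.

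- **Placement.** It follows the sentence on sensitivity analyses and most naturally elaborates it. The between-arm test is a mixed model, which can use incomplete repeated measures without imputation.
- **Algorithm.** The article does not say single imputation, EM or regression fill-in, nor that one completed data set is analysed as observed. The next sentence leaves the procedure open.
- **Other safeguards.** A dropout analysis is planned, selective dropout is to be taken into account, and the analysts are to be blind to condition.
- **Level of detail.** An article may leave missing-data details to a fuller document.
- **Simulation.** It is a single-outcome ANCOVA without group clustering, not the planned repeated-measures model, and the missing fractions are assumed.

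Most of this stands, and it rules out stronger readings that a reader might infer. The documents do not establish that the standard errors of the primary comparison will be too small, because no text sends filled values into it. They do not establish that intention-to-treat is breached: a reduced set is one reading of an ambiguous phrase, and under Discontinuation/modification of treatment patients are withdrawn only at their own request. Nor do they support a claim that the treatment difference would be pulled towards zero. That requires an imputation that leaves out the arm, and nothing in the text says so.

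What the reply does not remove is that the rule is stated, not left out. It is the only concrete method named, and following it as worded would give a worse analysis even in a sensitivity role. Point estimates could still be compared, but the intervals and p-values could not be relied on. The mixed model is not said to be fitted without filled values. Blinding limits a choice of method driven by the arms, but the choice would still be made after the data are seen.

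**Conclusion.** The point holds in conditional form. If the expected values are filled in once and analysed as observed, the standard errors of that analysis are too small: about 0.80 of the true value at an assumed 20% missing and about 0.70 at 30%, with type I error of about 12% and 17% against a nominal 5%. These figures rest on 86 and 146 patients, baseline adjustment with a correlation of 0.5, data missing completely at random and no clustering. They describe the rule as worded, not a demonstrated property of the primary test.

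Separately, the restriction to those remaining has to be reconciled with the intention-to-treat definition. Both should be settled before unblinding. The sample size of 232 is not affected.

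**What to change.** 1. Delete the expected-value rule.
2. State that the planned mixed model is fitted by likelihood to all observed EDE-Q scores of all randomised patients, with nothing filled in, and is valid under missing at random. Eligibility depends on the EDE-Q before and after phase 1 of CBT-E, so every randomised patient should have both scores.
3. As a first sensitivity analysis, use multiple imputation done separately by arm, including the pre- and post-phase-1 EDE-Q, respecting therapy group in the GST arm, and pooled with Rubin's rules.
4. As a second, use a delta-adjusted scenario in which patients with missing outcomes do worse than missing at random would predict.
5. Replace the reference to those remaining with all randomised participants.
6. Fix these choices before unblinding, in place of the sentence that lets the data obtained decide.

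The cost is a change of wording and a little more programming in R, which the article already plans to use. Confidence intervals will be wider than after a single fill-in, because they will reflect the information actually collected.
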